**Figure 2 figure2:**
[figure not shown]
Overview of the schedule for phase 3. ETS: exposure therapy specialist; FMS: Fast Motion Sickness Scale; SUDS: Subjective Units of Distress Scale; VR-ET: virtual reality exposure therapy.

#### Phase 3 Recruitment

Phase 3 will use the same recruitment methods as phase 1, including advertising through Epilepsy Toronto and using a snowball sampling strategy. In addition, phase 1 participants will be given the opportunity at the end of the questionnaire to enter their email address if they wish to receive more information about participating in phase 3.

Our target sample size for phase 3 is 5 people with epilepsy (people that do not have epilepsy themselves will not be included in phase 3). A sample size of n=5 was determined to be appropriate as this pilot study is evaluating feasibility of VR-ET for this population without aiming to determine clinical efficacy. In addition, sample size calculations are not necessary for feasibility studies according to the Consolidated Standards of Reporting Trials guidelines [31].

#### Phase 3 Consent and Eligibility

##### Overview

Participants will answer an eligibility screening after providing digital explicit consent through the phase 3 informed consent form (delivered over the Qualtrics platform). The eligibility screening will be completed over a telephone or video call with a member of the research team to help create rapport.

Even if the participant does not meet any of the exclusion criteria, they may be excluded from the study at any point. For example, if the research team is concerned that the treatment may have more negative consequences than positive for any reason, the principal investigator will consult with the ETS or make an executive decision to withdraw the participant from the study. However, information collected up until withdrawal may be (anonymously and in aggregate) included in the study analysis and findings. Participants are made aware of this in the phase 3 informed consent form.

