###### Exposure Session Timeline

Each participant will begin with the exposure scene that generates the least amount of anxiety and gradually work their way up to the scene that provokes the most anxiety. Each exposure scene will be performed daily for approximately 4 days, after which the participant will move onto the next level. However, if SUDS scores are >70 and at the discretion of the ETS, the current scene may be repeated until the participant is ready to progress. If a participant’s SUDS score is too high to begin the first level, they will be exposed to a different set and its associated scenes, even if it does not fit with their own anxiety as closely.

As such, the overall schedule may vary for each participant based on their individual progress. The participant is expected to complete the intervention in 12 days but will be allowed up to 14 days if additional days are required to complete a scene. If a participant has a seizure at any point during the 12 to 14 days that they are receiving the intervention, the VR-ET will be discontinued as a precautionary measure. However, data provided up until that point may still be used in analyses and they will participate in T2.

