#### Phase 3 Data Analysis

As both quantitative and qualitative data will be collected in phase 3, a mixed methods approach will be used. Quantitative statistical analyses will be performed using the MiniTAB statistical package [46] and SPSS software (version 27.0; IBM Corp) [47]. To investigate the normal data distributions of the dependent variables, ranges of skewness and kurtosis will be determined. The Kolmogorov-Smirnov and the Shapiro-Wilk tests will also be performed to evaluate statistical significance (mean, 95% CI) and normality of the distributions. In addition, Cronbach *α* will be performed for each self-report questionnaire’s subscales. To explore sociodemographic features, frequencies, means, and standard deviations will be calculated.

To explore the effects of VR-ET, data collected at T0 and T2 will be compared. Clinically significant effects of the intervention will be investigated using the Jacobson-Truax method, based on the measures’ clinical cut-offs (Table 2). Moreover, SUDS scores (before the exposure, immediately after the exposure, and 10 minutes after the exposure) collected every day of T1 will be compared with each other. Participants’ SUDS scores that are recorded immediately after the exposure may be lower than their anticipatory anxiety levels, and if so, this may encourage the participant to do the next exposure. We will also consider our study to be successful if participants’ SUDS scores remain high in the first postexposure SUDS test but decrease at the 10-minute postexposure SUDS test. However, the study may still be deemed successful with unchanging SUDS scores if participants have reduced anxiety and engage in fewer safety-seeking behaviors after completing VR-ET, as based on T2 findings.

Using thematic analysis, qualitative responses to assessments and interviews will be assessed by the research team and then reported as frequencies using the procedure outlined by Braun and Clarke [48]. The constant comparison method will be used to analyze the responses to the open-ended questions asked at T0 and T2 [49].

**Table 2 table2:** Clinically significant scoring for the phase 3 assessments.

		Items	Range	Scores	Citation

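### Withdrawal for perceived harm appears to end follow-up before T2, whereas a seizure stop keeps T2; the two rules should be reconciled

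*Protocol article*

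**What the plan says.** The protocol article describes two ways in which the team can stop a participant, and it treats follow-up differently in each.

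- **Perceived harm** (Phase 3 Consent and Eligibility, Overview). The trigger is broad: "if the research team is concerned that the treatment may have more negative consequences than positive for any reason". It can apply at any point. The consequence is that "the principal investigator will consult with the ETS or make an executive decision to withdraw the participant from the study". On data, the text says only that "information collected up until withdrawal may be (anonymously and in aggregate) included in the study analysis and findings". T2 is not mentioned.
- **Seizure during the intervention period** (Exposure Session Timeline). Here "the VR-ET will be discontinued as a precautionary measure". The participant is not withdrawn from the study: "However, data provided up until that point may still be used in analyses and they will participate in T2".

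EASI and PSS are repeated at T2, and IPQ, SUS and the semistructured exit interview take place only then (Table 1; Postintervention (T2)). The effect analysis rests on that visit: "To explore the effects of VR-ET, data collected at T0 and T2 will be compared". The sample is very small: "Our target sample size for phase 3 is 5 people with epilepsy".

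**The concern.** The seizure rule shows that the authors distinguish stopping the treatment from leaving the study. The perceived-harm rule does not make that distinction. If it is followed literally, whether a participant has T2 data depends on whether the team thought the treatment was hurting them. That is missingness related to outcome, and an analysis plan cannot recover measurements that were never taken.

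Two aims are exposed. Study Overview and Objectives places effect sizes and suggestions for improvement within the primary objective, and anxiety reduction as the secondary one. Effect sizes and anxiety reduction draw on the T0 to T2 comparison, and suggestions for improvement draw largely on the exit interview. Phase 3 Data Analysis also lets the study count as successful with flat SUDS scores if T2 shows less anxiety and fewer safety behaviours, so a success claim can rest on T2. People taken off because the therapy seemed to be going badly are the ones whose suggestions a larger trial most needs.

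**Working it through.** **No figure of the plan's own to reproduce.** The target of 5 is justified by feasibility and resources. No withdrawal rate, standard deviation or effect size is stated.

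**The two rules side by side**

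| | Perceived harm | Seizure |
|---|---|---|
| What ends | Participation in the study | VR-ET only |
| Earlier data | May be used | May be used |
| T2 | Not provided for | Attended |

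SUDS and Fast Motion Sickness Scale scores from sessions already held survive on both routes. What the perceived-harm route loses, on this reading, is T2 EASI, PSS, IPQ, SUS and the exit interview.

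**Share of T2 data lost.** With k such withdrawals out of 5 the share is k/5. One gives 1/5 = 20% (T2 on 4 of 5); two give 2/5 = 40% (T2 on 3 of 5).

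**Effect on a proportion improved (illustration).**
- One withdrawn, 3 of the remaining 4 improved: 3/4 = 75% among those with T2, against 3/5 = 60% of all five if the withdrawn person counts as not improved.
- Two withdrawn, all 3 remaining improved: 3/3 = 100% against 3/5 = 60%.

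**Effect on a mean change.** Let C be the mean change among those with T2 and W the mean change the withdrawn would have shown. The mean over all five is ((5 − k)C + kW)/5, so the completer mean differs from it by (k/5)(C − W). The gap between C and W is not in the documents. For assumed gaps of 5, 10 and 15 points on the 0–54 EASI:
- k = 1: 1, 2 and 3 points
- k = 2: 2, 4 and 6 points

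These figures show how the bias scales; they do not estimate it.

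**Chance that it arises at all.** This is 1 − (1 − p)^5 for an assumed per-person risk p of such a withdrawal. For p = 5%, 10%, 20% and 30% it is 23%, 41%, 67% and 83%. The protocol gives no value for p.

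**The case against.** The strongest reply is that the loss of T2 is read into silence. The perceived-harm text says what may be done with data already collected; it does not say that T2 is skipped. The article is condensed, and the full protocol may settle the matter. This stands in part: the loss is an inference. But the article is not silent on the rule itself. It withdraws the person from the study on one route, only stops treatment on the other, and promises T2 on the second alone.

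A reader might infer that the T0 to T2 result will omit the worst responders and rest on people who tolerated the therapy. The documents do not support that:
- Participants stopped for a seizure attend T2.
- Those who remove the headset early, or score above 70 on SUDS after an exposure, use coping mechanisms and still have their remaining scores recorded (Textbox 2). High scores can also lead to repeating a scene or using another set.
- Panic leads to contact with a health professional, with no withdrawal stated.
- The perceived-harm trigger is discretionary and can apply before any exposure, when the person is not a responder at all.

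What remains is a residual group that may be empty.

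Three further replies are sound. Jacobson-Truax classifies individuals, so one person's absence changes nobody else's classification; only a summary proportion can shift, and only if the withdrawn leave the denominator, which the article does not specify. A withdrawal would itself appear in the retention results, so it would not be hidden. And a reader might take the permissive wording on using earlier data as room for selective inclusion; that is conjecture, since it is ordinary consent language and nothing describes such a choice.

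The remaining reply, that this is an exploratory and uncontrolled pilot which disclaims clinical efficacy, limits the weight of any bias. It does not answer the loss of exit feedback, which serves the feasibility aim directly.

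**Conclusion.** The concern holds in limited form. As written, the two stopping rules are inconsistent on follow-up, and the route without T2 is the one triggered by perceived harm. A participant stopped on that route after starting exposure would contribute no T2 measures and no exit interview. The mean change or proportion improved could then lean towards benefit, and useful feedback would be lost.

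Each case costs 20% of the T2 data at the target of 5. Beyond that the size is unknown: the EASI shifts, responder percentages and withdrawal probabilities above all rest on assumed inputs. The conclusion assumes that withdrawal from the study means no T2 visit, and it matters only if such a withdrawal occurs after exposure has begun. It is a modest defect, worth correcting because lost T2 data cannot be recovered later.

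**What to change.** Reconcile the Overview under Phase 3 Consent and Eligibility with Exposure Session Timeline:

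1. State separately what it means to discontinue VR-ET and what it means to withdraw from the study.
2. Invite every participant with at least one exposure session who stops VR-ET, for any reason, to the full T2 (EASI, PSS, IPQ, SUS and exit interview) one week after the last exposure, unless they withdraw consent or decline.
3. Report T0 to T2 summaries over all participants who started exposure, showing how many lack T2 and by which route they stopped.

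This leaves untouched the decision on when treatment should stop. Table 1 already times T2 from the final exposure session, and only equipment collection at T2 is in person, so the change extends an existing arrangement. The cost is amended protocol and consent wording plus a few extra remote contacts, which participants may decline.

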##### Phase 3 Inclusions

Individuals with diagnosed epilepsy aged 18-65 years with self-reported mild or moderate epilepsy-related anxiety may participate in this study.

##### Phase 3 Exclusions

ET works by increasing anxiety in the short-term for the purpose of decreasing anxiety in the long-term. Because it is expected that participants’ anxiety will rise during the ET sessions, anyone who was told by a neurologist or personally believes that stress has provoked their seizures in the past will be excluded from phase 3. Anyone with a self-reported diagnosis of panic disorder or self-reported severe epilepsy-related anxiety will also be excluded from this pilot study. However, should VR-ET for people with epilepsy become a standard treatment, people whose seizures are triggered by stress should decide with their medical team if the benefits of this treatment outweigh the risks. Therefore, people with epilepsy should consider whether a long-term decrease in stress from VR-ET (and a consequent decrease in seizures triggered by stress) may be worth the short-term increase in stress and the accompanying risk of seizures.

Those who have been told by a neurologist that they have photosensitivity or that they have had photoparoxysmal responses during an electroencephalogram will also be excluded from phase 3 [15]. Excluding people with photosensitivity from the study is not expected to significantly impact the sample size because only approximately 3% to 5% of people with epilepsy have photosensitive seizures [32]. However, even individuals who were never told by a neurologist that they have had photosensitive seizures but believe that photosensitivity may contribute to their seizures will also be excluded from phase 3 [15]. Similarly, individuals who previously experienced seizures after being in a VR environment will also be excluded from this study.

As depression and anxiety are common in people with epilepsy [2], many people that are interested in participating in the study may be taking psychotropic medications, such as antidepressants. Because antidepressants may take up to 12 weeks to show their full effects, it would be unclear whether improvements in anxiety from baseline are due to a response to medication or VR-ET [33]. Similarly, drugs such as benzodiazepines, which are used to treat seizures, may act to suppress the anxiety felt by people with epilepsy during VR-ET [34]. Therefore, to better evaluate the impact of VR-ET alone, people who began taking antidepressants, benzodiazepines, or medical marijuana within 12 weeks of phase 3 will be excluded.

Although individuals will not be excluded from the study if they have been taking benzodiazepines for longer than 12 weeks before starting phase 3, they will be asked to avoid taking them before the exposure session (only if possible and if it does not interrupt their antiseizure medication schedule). This is because benzodiazepines have immediate effects and may therefore artificially lower participants’ SUDS scores [35]. A complicating factor in this regard is that some people with epilepsy are prescribed drugs such as benzodiazepines as a rescue medication and may therefore use them to stop or prevent seizures [34,36]. In clinical practice, it is possible that the patient may take a benzodiazepine before, during, or after performing an exposure solely out of fear that they will have a seizure (and not necessarily because they are actually about to have a seizure). In this case, the patient would be actively avoiding the anxiety that is associated with the exposure. By using avoidance, the exposure’s usefulness is nullified because the patient is shielded from feelings of fear. They also momentarily lose the opportunity to learn that they are capable of handling these feelings of anxiety.

Other phase 3 exclusion criteria include individuals who have tonic-clonic seizures more than once a month, individuals who have functional seizures, individuals who cannot speak or understand English, individuals with open wounds on their face, and individuals with cervical conditions or injuries that would make it unsafe for them to use an HMD.

We will not be excluding individuals with memory deficits, as memory issues are common in people with epilepsy [37]. It is not a concern that memory difficulties will prevent participants from using the VR device properly as they will always be on a video call with a member of the research team who can guide the participant in using the VR headset as necessary.

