**Background questionnaire**
This questionnaire was created by the authors of this paper to be conducted at the baseline interview (Textbox 4). Its main purpose is to collect phase 3 participants’ demographic information and information about their history with anxiety and epilepsy.

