We acknowledge that it may not be feasible in clinical practice for therapists to have daily communication with their clients or patients. However, we are designing the intervention this way purposefully for the pilot study to maximize safety in case of a seizure or concerning psychological distress, such as a panic attack. In addition, as discussed with a clinical neuropsychologist, it will maximize the chances of therapeutic success if participants are in communication with someone, such as a therapist or researcher, while doing the exposures to help them form a behavioral commitment. Because this is a pilot study, it aligns more with the purpose of the research to maximize the chances of therapeutic success rather than to assess the feasibility of the proposed intervention within a professional setting. However, the ability to implement self-guided sessions in a controlled and safe virtual environment is an advantage of VR therapy. Therefore, future studies should investigate participants’ adherence to VR-ET and its efficacy when they perform the exposures daily without a researcher or therapist present.

Another limitation is that while we ask participants to avoid taking a benzodiazepine before performing the exposure and after their exposure until their anxiety settles, we cannot enforce this request because benzodiazepines may be used to treat seizures [34]. As previously discussed, taking a benzodiazepine can limit the effectiveness of the ET. It may be worthwhile to conduct future clinical trials in a safe and well-monitored environment, such as a hospital epilepsy monitoring unit, where participants are restricted from taking a benzodiazepine as much as possible. In this scenario, the participants would be in a safe environment in case they were to have a seizure and potential confounding effects would be reduced.

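### The 12-week medication exclusion catches only people who started one of three drug types, so a recent dose change or stop of the same drugs passes it

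*Protocol article*

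**What the plan says.** The protocol article gives the reason and the rule together, under Phase 3 Exclusions. The reason is that "antidepressants may take up to 12 weeks to show their full effects", so that "it would be unclear whether improvements in anxiety from baseline are due to a response to medication or VR-ET". It adds that benzodiazepines may damp the anxiety felt during sessions. The rule, introduced as a means "to better evaluate the impact of VR-ET alone", is that "people who began taking antidepressants, benzodiazepines, or medical marijuana within 12 weeks of phase 3 will be excluded".

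The same section shows that the window looks back from entry: people are kept "if they have been taking benzodiazepines for longer than 12 weeks before starting phase 3", with a request to avoid the drug before a session where possible. The Limitations section says of that request that "we cannot enforce this request because benzodiazepines may be used to treat seizures".

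Current antiseizure drugs, anxiety as a side effect of them, medical marijuana, and antidepressants or other anti-anxiety drugs are asked about in the background questionnaire. Of its timing the article says: "This questionnaire was created by the authors of this paper to be conducted at the baseline interview". Table 1 and the Postintervention (T2) section list no medication item at T2.

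The comparison at issue is in Phase 3 Data Analysis: "To explore the effects of VR-ET, data collected at T0 and T2 will be compared". Clinical significance is then assessed by the Jacobson-Truax method. There is no control group.

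**The concern.** The rule is narrower than its own reason. The worry is that a drug effect still developing at T0 would be read as a VR-ET effect at T2. Starting a drug is one way for that to happen. Changing the dose of the same drug, or stopping it, shortly before T0 is another. Read literally, as a screener would read it, the word *began* admits both.

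At stake is the secondary objective, whether VR-ET reduces epilepsy-related anxiety, and the effect sizes that the study objectives say will be determined for planning a larger trial. With no control arm, nothing in the comparison subtracts a drug-driven change. The bias could go either way: a recent dose change could produce an apparent benefit, and a recent stop could mask a real one. Because Jacobson-Truax classifies individuals, a single drug-driven change could also put that participant in the wrong category, whatever happens to the mean.

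**Working it through.** The plan derives no figure on this point, so there is nothing to reproduce. The check is mainly one of wording, with some arithmetic for scale.

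**1. Rule against reason, for the three named drug types in the 12 weeks before phase 3**

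| Event | Caught by the rule? | Does the stated attribution problem apply? |
|---|---|---|
| Drug started | Yes | Yes |
| Dose changed | No | Yes |
| Drug stopped | No | Yes |

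No other section closes the second and third rows. The request about benzodiazepines concerns use around sessions. The general discretion to withdraw participants, under Phase 3 Consent and Eligibility, is illustrated by harm outweighing benefit. Neither asks for stable medication.

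**2. Time scale**

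Inputs: 12 to 14 daily sessions (Exposure Session Timeline), T2 one week after the last session (Postintervention), and up to 12 weeks for full antidepressant effect (Phase 3 Exclusions).

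- T0 to T2, at least about: 12 + 7 = 19 days, up to 14 + 7 = 21 days.
- Share of the 12-week (84-day) period: 19/84 = 23%, 21/84 = 25%.
- Illustration: an antidepressant dose changed 14 days before T0 is 14 + 19 = 33 to 14 + 21 = 35 days old at T2, about week 5 of 12. The whole T0-T2 interval then lies inside the period that the protocol regards as unsettled.

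**3. Effect on the mean**

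With n = 5 (Phase 3 Recruitment), a drug-driven change of d points in one participant shifts the mean change by d/5. The documents give no value for d. Assumed EASI values, on its 0-54 range:

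- d = 3: 3/5 = 0.6 points
- d = 5: 5/5 = 1.0 point
- d = 10: 10/5 = 2.0 points

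**4. Chance of at least one affected participant**

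If each participant independently has probability p of an uncovered change, the chance of at least one among 5 is 1 − (1 − p)^5. The documents give no p. Assumed values:

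| p | Chance of at least one in 5 |
|---|---|
| 2% | 9.6% |
| 5% | 22.6% |
| 10% | 41.0% |
| 20% | 67.2% |

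Steps 3 and 4 show scale only. They are not evidence that the bias will occur.

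**The case against.** The strongest reply is that this is an open-label pilot of 5 people whose main purpose is feasibility. The article says more than once that it does not aim to establish clinical efficacy. Even a perfect medication criterion would leave regression to the mean, expectancy and unblinded self-report, and the rule itself claims only to improve the evaluation. This stands, and it sets the severity. It does not remove the point: the article still plans the T0-T2 comparison and the Jacobson-Truax classification, allows T2 findings to bear on whether the study counts as successful, and judged this particular confounder worth an exclusion.

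Several stronger readings are tempting, and the documents do not support them:

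- **That the rule is defective because it misses drugs started after T0.** An entry criterion cannot govern what happens after entry. What remains is that such starts would be useful to record at T2.
- **That medication dates are not collected.** The background questionnaire is shown only in outline, and the items of the separate eligibility screen are not shown. The rule cannot be applied without asking when a drug was started. A fuller protocol may also hold a medication log.
- **That every antiseizure-drug change and all cannabis use should be exclusions.** The article treats anxiety from antiseizure drugs as relevant. Excluding on any change in them, in an epilepsy population and with 5 places to fill, is a trade-off against recruitment feasibility, which is itself a primary goal. Starting a benzodiazepine is already covered.
- **That a 12-week lag holds for all drugs and all kinds of change.** The article grounds that lag only for antidepressants and describes benzodiazepine effects as immediate. The protocol does, however, apply its 12-week window to all three named types, so keeping that window for dose changes and stops of those types adds no new claim about lag.

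**Conclusion.** The concern holds in a narrow form and is minor. For the drug types it names, the exclusion covers starting but not dose changes or stopping, although the protocol's own reason for the window applies to all three. A person with such a recent change can enter, and the change can then be mistaken for, or can hide, a VR-ET effect over a T0-T2 interval of at least about 19 to 21 days.

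The conclusion rests on the wording of a criterion that the article states in full. It does not rest on any estimate of how often this happens or how large the effect is, since the documents give neither. The shift of 0.6 to 2.0 EASI points in the mean follows from assumed individual changes of 3 to 10 points and one affected participant in 5. A reader might infer that the T0-T2 result is confounded. The documents support only that it can be, and tightening the rule would not make the change attributable to VR-ET in a study without controls.

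**What to change.** 1. Reword the criterion to exclude people who *started, stopped or changed the dose of* an antidepressant, a benzodiazepine or medical marijuana within 12 weeks before T0. This keeps the drug types and window already chosen. It concerns eligibility only and alters no one's treatment.
2. For the other drugs that the background questionnaire treats as relevant (antiseizure drugs and other anti-anxiety drugs), record recent changes at T0 instead of excluding.
3. Repeat the medication question at T2.
4. In the individual T0-T2 and Jacobson-Truax results, flag any participant whose medication changed shortly before T0 or between T0 and T2.

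The cost is a few words in the criterion, a note of recent changes at T0 and one question at T2. A few otherwise eligible people may be deferred, which could slow recruitment to 5; the documents give no basis for saying how many. If that is unacceptable, steps 2 to 4 alone, with recent changes in the three named drug types also recorded at T0, would make the problem visible without narrowing entry.
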